### Blinding

Blinding may prove costly, logistically challenging, and technically difficult in our setting. Therefore, we opt to carry out an open randomized controlled trial.

### Interventions

Patients will be allocated to the indomethacin/nifedipine combination group or the nifedipine monotherapy group for 48 h. In the nifedipine group, the patients will receive 20 mg oral nifedipine. If contraction inhibition occurs for 2 h, the patients will continue to receive 20 mg of oral nifedipine every 4 h for 48 h, and the maximum dose will not exceed 180 mg per day. In the combination group, the patient will be administered nifedipine orally, as in the monotherapy group, and 100 mg indomethacin rectally. In the case of contraction inhibition after 2 h, the patients will receive 25 mg of oral indomethacin every 4 h. The maximum daily dosage of indomethacin will not exceed 200 mg/day, and the maximum duration will be 48 h. Terbutaline hydrochloride (the second-line drug) will be used in those cases (in both arms) of unsuccessful treatment and if there is no contraindication for terbutaline. Terbutaline hydrochloride will be used by intravenous drip, adjusted for its effectiveness in inhibiting uterine contractions [21]. Four doses of 6 mg dexamethasone will be given intramuscularly every 12 h [22].

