### Sample size

Each study group will consist of 117 women, a number calculated based on a previous study [17]. We expect the proportion of successful outcomes (the number of women who do not deliver and who do not need alternative treatment for 48 h) in nifedipine monotherapy to be 72.0%, and we expect it to be 89.0% in the combination group. This sample size (117 in each arm) was necessary to achieve a 95% confidence level with a 5% margin of error and 80% power.

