### Outcome measurements

#### Primary outcomes

The monitoring of uterine contractions will be performed continuously by an external tocodynamometer for 2–4 h after the first administration of the study’s medications followed by two to three times per day for 30–60 min. The primary outcome will be an estimation of the tocolytic effectiveness and safety profile. The effectiveness will be assessed in terms of the proportion of women who do not deliver and who do not need alternate tocolytic medication (terbutaline) within 48 h after the first administration of the study drug. Safety assessment will be performed by assessing maternal-associated adverse effects that include maternal tachycardia (i.e., a heart rate above 120 beats per minute), hypotension (i.e., systolic blood pressure less than 90 mmHg), and other symptoms, such as palpitations, headache, nausea, vomiting, itching, and rash.

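### In the first 24 h the indomethacin schedule gives 225–250 mg, above the stated 200 mg daily maximum, and no rule says which prevails

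*Protocol article*

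**What the plan says.** All the dosing rules are in the Interventions section of the protocol article. Women in the combination arm receive nifedipine as in the other arm, plus "100 mg indomethacin rectally". For those who respond, the maintenance rule is: "In the case of contraction inhibition after 2 h, the patients will receive 25 mg of oral indomethacin every 4 h". The ceiling follows immediately: "The maximum daily dosage of indomethacin will not exceed 200 mg/day, and the maximum duration will be 48 h".

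The same paragraph also sets a ceiling for nifedipine: "the maximum dose will not exceed 180 mg per day".

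The article does not say whether the rectal dose counts toward the indomethacin ceiling, how a day is counted, or which oral doses to hold if the ceiling is reached.

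**The concern.** A fixed schedule and a fixed ceiling for the same drug should be compatible for a woman who takes the full course. Here they appear not to be during the first 24 h, so ward staff would have two instructions and no stated way to choose between them. Following the schedule exceeds a stated dose limit and is a protocol deviation. Following the ceiling means leaving out scheduled doses without a rule for which ones or for how long.

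Indomethacin is the only planned difference between the arms, so the ambiguity concerns the experimental treatment itself. The point of divergence also lies inside the primary outcome window, which runs "within 48 h after the first administration of the study drug", and maternal safety is part of that primary outcome.

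**Working it through.** **Inputs (Interventions section).** Rectal dose 100 mg, taken as time 0. Oral dose 25 mg every 4 h. Ceiling 200 mg per day. Treatment lasts up to 48 h. The time of the first oral dose is not fixed beyond following a 2 h response check, so 2, 4 and 6 h were all tried.

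**First 24 h.** Total = 100 + 25 × (number of oral doses from time 0 to just before 24 h).

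| First oral dose | Oral dose times (h) | Oral total | With rectal dose | Over 200 mg |
|---|---|---|---|---|
| 2 h | 2, 6, 10, 14, 18, 22 | 6 × 25 = 150 mg | 250 mg | 50 mg (25%) |
| 4 h | 4, 8, 12, 16, 20 | 5 × 25 = 125 mg | 225 mg | 25 mg (12.5%) |
| 6 h | 6, 10, 14, 18, 22 | 5 × 25 = 125 mg | 225 mg | 25 mg (12.5%) |

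With a first oral dose at 4 h, a dose also falls exactly at 24 h. Counting it in the first day makes that row 250 mg.

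**When the ceiling is passed.** (200 − 100) / 25 = 4 oral doses fit. The fifth, at 18, 20 or 22 h, is the first to exceed it.

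**Second 24 h.** Six oral doses = 150 mg in each case, within the ceiling.

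**Other readings.**
- Rectal dose not counted: 125–150 mg in the first 24 h, so no conflict.
- Calendar day: the fifth oral dose falls before midnight only if treatment starts before 24 − 18 = 06:00, 24 − 20 = 04:00 or 24 − 22 = 02:00. If starts are spread evenly over the day, that is 25%, 16.7% or 8.3% of women.

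**Women reached.** The Sample size section states "we expect it to be 89.0% in the combination group", where success means undelivered and without alternative tocolysis at 48 h. 117 × 0.89 = 104.1, so about 104 women would still be on schedule at the fifth oral dose, assuming none stops indomethacin early for intolerance. On the calendar-day reading, 104.1 × 0.25, 0.167 and 0.083 give about 26, 17 and 9 women.

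**If the ceiling overrides and the 4 h clock is kept.**

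| First oral dose | Last dose before hold | Doses held | Next dose | Gap | 48 h total as scheduled | 48 h total capped |
|---|---|---|---|---|---|---|
| 2 h | 14 h | 2 | 26 h | 12 h | 250 + 150 = 400 mg | 200 + 150 = 350 mg |
| 4 h | 16 h | 1 | 24 h | 8 h | 225 + 150 = 375 mg | 350 mg |
| 6 h | 18 h | 1 | 26 h | 8 h | 225 + 150 = 375 mg | 350 mg |

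**Comparison with nifedipine.** On the same count, the first 24 h give 20 + 6 × 20 = 140 mg or 20 + 5 × 20 = 120 mg, against a 180 mg ceiling. That ceiling is never reached, so it gives no precedent for how a collision should be handled.

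**The case against.** The strongest reply is that a ceiling stated after a schedule limits the schedule. The wording is mandatory, so once 200 mg is reached the next dose is simply not given. On that reading the arm can be delivered, and only staff who ignored the ceiling would deviate. What would remain is operational detail (which dose to hold, when to restart, how to count a day) that an article may leave to the full protocol.

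Part of this stands. The override reading is workable, and the rectal-dose and calendar-day readings are possible. It also stands that the 8–12 h gap concerns oral indomethacin only, because nifedipine continues every 4 h in both arms, and that the regimens differ by only 25–50 mg over 48 h.

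The reply does not remove the conflict. Under the override reading, the printed 4-hourly schedule cannot be given as written to any responder who completes the first 24 h. The ceiling applies to the drug without excluding a route, so leaving out the rectal dose has to be read into the text. On a calendar-day reading, the same regimen complies or not according to the hour treatment starts. The article prints both rules and they disagree on the plain reading, which is different from detail left out for brevity.

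**Conclusion.** The concern holds. If the rectal dose counts and a day is 24 h from the first dose, the indomethacin schedule exceeds its own ceiling by 25–50 mg (12.5–25%) in the first 24 h for every first oral dose time tried. It affects responders who stay on treatment to 18–22 h, about 104 of 117 on the protocol's planning assumption and with no early stopping for intolerance. The second 24 h complies.

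The consequence is contained. Nothing in the article shows that the extra 25–50 mg causes harm or would shift the 48 h outcome. Randomisation, sample size and the intention-to-treat analysis do not depend on it. It should still be fixed, because staff need one unambiguous rule for a stated safety limit on the only drug that differs between the arms.

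**What to change.** Before dosing, the clinical investigators should amend the Interventions paragraph, and any dosing sheet used on the ward, so that the schedule and the ceiling agree. A day should be defined as 24 h from the first dose. Three options work arithmetically:

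1. Limit the first 24 h to four 25 mg oral doses after the rectal dose (100 + 4 × 25 = 200 mg) and state when dosing resumes. This keeps every stated dose amount and limit, at the price of an 8–12 h gap in oral indomethacin if the 4 h clock is kept.
2. Lengthen the oral interval to 6 h. The first 24 h then total 200 mg (first oral dose at 2 or 4 h) or 175 mg (at 6 h).
3. State that the ceiling excludes the rectal loading dose. The schedule then stands unchanged.

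The choice is clinical; option 1 departs least from the stated doses and limit. If dosing has already begun, the same clarification applies, with a record of which rule was followed. The cost is a one-paragraph amendment and an updated dosing sheet. Sample size, endpoints and analysis do not change.

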### Outcome measurements

#### Primary outcomes

The monitoring of uterine contractions will be performed continuously by an external tocodynamometer for 2–4 h after the first administration of the study’s medications followed by two to three times per day for 30–60 min. The primary outcome will be an estimation of the tocolytic effectiveness and safety profile. The effectiveness will be assessed in terms of the proportion of women who do not deliver and who do not need alternate tocolytic medication (terbutaline) within 48 h after the first administration of the study drug. Safety assessment will be performed by assessing maternal-associated adverse effects that include maternal tachycardia (i.e., a heart rate above 120 beats per minute), hypotension (i.e., systolic blood pressure less than 90 mmHg), and other symptoms, such as palpitations, headache, nausea, vomiting, itching, and rash.

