### Patients

Inclusion criteria: women aged 18–40 years with a viable fetus diagnosed with threatened PTL and whose gestational age is between 25 and 34 weeks will be eligible for participation in this trial. A diagnosis of threatened PTL will be defined as persistent uterine contractions “(four contractions every 20 min or eight every 60 min)” with cervical changes “(cervical effacement ≤80% or cervical dilatation > 2 cm) [20]. Patients are eligible independent of the presentation of the fetus.Exclusion criteria: Women who have had multiple pregnancies; any condition considered as a contraindication for tocolysis, e.g., hypertension or the use of anti-hypertensive medication, ruptured membranes, signs of fetal distress and/or intrauterine infection; a maternal temperature > 38 °C; severe vaginal bleeding; myocardial infarction within 3 months; unstable angina pectoris; cervical dilatation of more than 5 cm; cerclage; suspicion of neonatal chromosomal or structural anomalies; tocolytic treatment for more than 6 h prior to arriving in the participating hospital; and an unwillingness to participate in this study.

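### The maternal safety outcome does not separate events before and after rescue terbutaline, which may be commoner on monotherapy; recording onset would be a cheap improvement

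*Protocol article*

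**What the plan says.** The Primary outcomes section of the protocol article names both effectiveness and safety as primary. Effectiveness is "the proportion of women who do not deliver and who do not need alternate tocolytic medication (terbutaline) within 48 h", counted from the first dose. Safety is described separately: "Safety assessment will be performed by assessing maternal-associated adverse effects that include maternal tachycardia (i.e., a heart rate above 120 beats per minute", then systolic pressure below 90 mmHg and symptoms such as palpitations, headache, nausea, vomiting, itching and rash. The 48 h window belongs to the effectiveness sentence. The safety sentence has no window, no link to a particular drug and no rule for events after rescue.

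Under Interventions, terbutaline "will be used in those cases (in both arms) of unsuccessful treatment and if there is no contraindication for terbutaline". The same section adds: "Terbutaline hydrochloride will be used by intravenous drip, adjusted for its effectiveness in inhibiting uterine contractions".

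Under Sample size, the expected proportion free of both delivery and alternative treatment is given as "in nifedipine monotherapy to be 72.0%, and we expect it to be 89.0% in the combination group".

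The Analysis section specifies intention to treat and an NNH for adverse outcomes. The Background states tolerability of the combination against monotherapy as part of the aim.

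**The concern.** Need for terbutaline is one of the two ways to fail the effectiveness outcome. It also exposes the woman to a further tocolytic, given intravenously and titrated to effect. Terbutaline is a beta-agonist, so it may plausibly produce some of the listed effects, tachycardia and palpitations above all. Under intention to treat, an effect that starts during the drip counts against the randomised arm.

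If the combination works as planned, fewer of its women reach the drip, and its adverse-effect count falls for that reason alone. The tolerability comparison would then partly repeat the effectiveness result. What is at stake is how the NNH is read. A reader is likely to take it as the cost of adding indomethacin, whereas it would describe study drug and rescue together. If onset is not captured at the bedside, no later analysis can separate the two.

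**Working it through.** **Inputs from the protocol.** Expected success is 72.0% on monotherapy and 89.0% on the combination, with 117 women per arm (Sample size). Failure is delivery or need for terbutaline within 48 h (Primary outcomes).

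**Assumptions, not in the protocol.** b is the event rate on study drug, equal in both arms, at 5% or 10%. q is the event rate caused by terbutaline among rescued women, 10% to 50%, independent of b. s is the share of failures that receive terbutaline, 1 or 0.5, the same in both arms.

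**Step 1: composite failure.**
- Monotherapy: 1 − 0.72 = 0.28, and 117 × 0.28 = 32.8, about 33 women.
- Combination: 1 − 0.89 = 0.11, and 117 × 0.11 = 12.9, about 13 women.
- Ratio: 0.28 / 0.11 = 2.55.

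**Step 2: from failure to rescue.** Some failures may be deliveries without terbutaline. If these make up d_m of the monotherapy arm and d_c of the combination arm, the rescue ratio is (0.28 − d_m) / (0.11 − d_c).

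| d_m | d_c | Rescue ratio |
|---|---|---|
| 0 | 0 | 0.28 / 0.11 = 2.5 |
| 14% | 5.5% | 0.14 / 0.055 = 2.5 |
| 5% | 5% | 0.23 / 0.06 = 3.8 |
| 20% | 3% | 0.08 / 0.08 = 1.0 |

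So 28% and 11% are ceilings on 48 h rescue use at the planned rates. The ratio of 2.5 holds if rescue takes the same share of failures in each arm.

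**Step 3: effect on the safety count.** With failure rate f, the counted rate is b + (1 − b) × s × f × q. With no true difference between regimens, the gap is (1 − b) × s × q × (0.28 − 0.11).

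| s | b | q | Monotherapy | Combination | Gap (points) |
|---|---|---|---|---|---|
| 1 | 10% | 10% | 12.5% | 11.0% | 1.5 |
| 1 | 10% | 30% | 17.6% | 13.0% | 4.6 |
| 1 | 5% | 30% | 13.0% | 8.1% | 4.8 |
| 1 | 5% | 50% | 18.3% | 10.2% | 8.1 |
| 0.5 | 10% | 10% | 11.3% | 10.5% | 0.8 |
| 0.5 | 5% | 30% | 9.0% | 6.6% | 2.4 |
| 0.5 | 5% | 50% | 11.7% | 7.6% | 4.0 |

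For example, in the second row: 0.10 + 0.90 × 0.28 × 0.30 = 0.176 against 0.10 + 0.90 × 0.11 × 0.30 = 0.130.

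**Step 4: scale against precision.** For 17.6% against 13.0% with 117 per arm, the standard error is √[(0.176 × 0.824 + 0.130 × 0.870) / 117] = 0.047. The 95% half-width is 1.96 × 0.047 = 9.2 points, so a 4.6-point shift is about one standard error.

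**Step 5: a true excess on the combination.** Suppose the combination adds 3 points to b for the same effect. The displayed difference (combination minus monotherapy) then runs from +2.2 points (s = 0.5, b = 5%, q = 10%: 8.5% against 6.3%) to −5.2 points (s = 1, b = 5%, q = 50%: 13.1% against 18.3%).

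**The case against.** The strongest reply is that counting every event by randomised arm is a legitimate comparison. Terbutaline is the specified second line in both arms. If the combination spares women a drip and its effects, that is a real benefit of the strategy. This stands, and the all-events comparison should be kept. It misleads only when read as tolerability of the study drugs themselves.

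A second reply is that cutting off events at rescue brings its own bias. Rescue happens after randomisation and differs by arm. Response is judged at 2 h, so an early failure could contribute about 2 h at risk rather than 48 h, and this would happen more often on monotherapy. This also stands. The pre-rescue comparison should sit beside the main one with time at risk shown, and should not replace it.

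A third reply is that onset fields and attribution rules usually belong in the case report form or analysis plan, which are not shown. That is fair, and it is why this is an improvement and not an error. The definition as published, however, leaves the two sources of events mixed in a primary outcome.

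Four stronger readings are tempting, and the protocol does not support them:
- A reader might infer that the plan expects terbutaline 2.5 times as often on monotherapy. It states only composite failure, and women with a contraindication receive none.
- A reader might infer that the combination will look better tolerated than it is. That depends on a terbutaline event rate that the protocol does not give and on the true effect of indomethacin (Step 5).
- A reader might infer that an excess of nausea or vomiting from indomethacin would be cancelled by tachycardia on terbutaline. The effects are listed separately and no pooled any-event measure is defined.
- A reader might infer bias from admitting women with shorter prior tocolysis, since the exclusion is only "tocolytic treatment for more than 6 h prior to arriving in the participating hospital". That exposure precedes randomisation and is balanced between arms in expectation.

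**Conclusion.** The point holds as a cheap improvement. As published, the safety outcome mixes tolerability of the study drugs with exposure to rescue, and the plan's own failure rates of 28% and 11% suggest more rescue on monotherapy. With more rescue on monotherapy, any effect caused by terbutaline pushes the count in favour of the combination.

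The shift is about 1.5 to 8 points if every failure is rescued and about 0.8 to 4 points if half are. These figures assume terbutaline event rates of 10% to 50%, study-drug rates of 5% to 10% equal in both arms, and the same share of failures rescued in each arm. The shift would vanish if rescue were equally common in both arms, as in the 20% and 3% delivery split of Step 2. The direction is therefore likely under the planned effect but not certain, and the size rests on rates that the protocol does not give.

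**What to change.** - Record the onset time of each maternal adverse effect relative to the first study dose and to any start of terbutaline.
- Keep the intention-to-treat comparison of all events, and its NNH, as the whole-strategy result. State that this NNH reflects the strategy including rescue.
- Beside it, report for each listed effect the proportion of randomised women with onset after the first study dose and before any terbutaline. Show time at risk or time to rescue by arm.

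The cost is one form field and one extra table. The pre-rescue comparison has a shorter time at risk that depends on the arm, so it must be read with that time shown. No change to treatment or to the use of rescue is involved.

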#### Secondary outcomes

Secondary outcomes will be the number of women with preterm birth before 37 weeks, women with preterm birth before 34 weeks, days until delivery, gestational age at delivery, neonatal morbidity and mortality related to prematurity (e.g., lung disease, severe intraventricular hemorrhage, periventricular leukomalacia, sepsis, necrotizing enterocolitis), and gestational age at delivery. These outcomes will be assessed by the neonatologist (with suitable/optimum investigations) until discharge from the hospital or neonatal death.

### Follow-up of women and infants

The delivery details, pregnancy and postpartum assessments for both mothers and neonates will be recorded in a hospital-based case follow-up form. In addition, all details of neonatal admission will be recorded.

### Analysis

Statistical analysis will be performed by using the SPSS version 22.0 (IBM) program (intention-to-treat analysis). In the evaluation of the study data, descriptive statistical methods (mean, standard deviation, minimum, maximum, median, frequency, and ratio) will be used. Student’s *t*-test will be used to compare quantitative data for normally distributed data, and if the distribution is not consistent with a normal distribution, the Mann–Whitney *U* test will be used to compare the variables between women in each arm of the study. Pearson’s chi-squared and Fisher’s exact tests will be used for qualitative data comparisons. Number needed to treat (NNT) for benefits and number needed to harm (NNH) for adverse outcomes with their 95% confidence outcomes will be calculated. A *p*-value> 0.05 will be considered statistically significant.

The groups (nifedipine/indomethacin combination group or nifedipine monotherapy group) will be analyzed as group A and group B, and confidentiality will be preserved. The identification of groups will be revealed only after the analysis is finished with the tables ready.

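### Gestational age at delivery is compared without adjusting for gestational age at entry: a valid test, but one that gives up precision the trial could have for free

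*Protocol article*

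**What the plan says.** All places are in the protocol article.

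- **Analysis.** Quantitative data go to Student's t-test, which "will be used to compare quantitative data for normally distributed data". For other distributions the Mann-Whitney "test will be used to compare the variables between women in each arm of the study". No covariate and no time-to-event method is named. The analysis is by intention to treat.
- **Secondary outcomes.** The list includes "women with preterm birth before 34 weeks, days until delivery, gestational age at delivery". Two of these are quantitative, so the rule above covers both.
- **Patients.** Women are eligible "whose gestational age is between 25 and 34 weeks", a 9-week range.
- **Procedures, randomization, recruitment, and collection of study data.** Allocation is in blocks of 8. No stratification by gestational age is mentioned.
- **Follow-up of women and infants.** Delivery details "will be recorded in a hospital-based case follow-up form". The article gives no expected loss and no rule for a woman whose delivery date is unknown.

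**The concern.** Gestational age at delivery is an exact sum: gestational age at entry plus the time from entry to delivery. Treatment can act only on the second part. The first is fixed before randomisation, varies over 9 weeks, and must be known for every woman because it decides eligibility. A two-sample test leaves it in the error term. Any chance difference in entry age between the arms then passes, wholly or in part, into the observed difference in delivery age.

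What is at stake is the precision of one secondary outcome. A real prolongation of pregnancy could be blurred, or the gestational-age result could seem to disagree with the latency result only because the arms differed by chance at entry.

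A second, conditional matter concerns days until delivery. Neither named test can use a woman with no known delivery date: she must be dropped or given a value.

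**Working it through.** **The plan's own figure.** The article gives no SD, effect size or power for either outcome. Its 117 per arm is derived for the binary primary outcome (72.0% vs 89.0%, 5% error, 80% power). A standard two-sided calculation with those inputs gives 85 per arm (96 with continuity correction), so 117 is not reproduced. That is a separate matter; here 117 is only the number per arm.

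**Step 1: spread at entry.** Assume entry uniform on 25-34 weeks. SD = 9/√12 = 2.60 weeks, variance 6.75. The difference in mean entry age between arms has SD 2.60 × √(2/117) = 0.34 week, or 2.4 days.

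**Step 2: share of variance due to entry age.** Let latency change by b weeks per week of entry age, with residual SD s (both assumed). Then

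ρ² = (1+b)² × 6.75 / [(1+b)² × 6.75 + s²]

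| b | s = 2 | s = 3 | s = 4 |
|---|---|---|---|
| 0 | 6.75/10.75 = 0.63 | 6.75/15.75 = 0.43 | 6.75/22.75 = 0.30 |
| −0.5 | 1.69/5.69 = 0.30 | 1.69/10.69 = 0.16 | 1.69/17.69 = 0.10 |

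**Step 3: effect of adjustment.** ANCOVA multiplies the variance of the treatment difference by 1 − ρ², so 117 per arm acts like 117/(1 − ρ²) unadjusted:

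- ρ = 0.3: factor 0.91, like 129 per arm
- ρ = 0.5: factor 0.75, like 156
- ρ = 0.7: factor 0.51, like 229

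**Step 4: check with a different latency model.** This simulation used 117 per arm and uniform entry. Early delivery was 28% vs 11% (the complements of 72% and 89%, borrowed as an assumption because failure there also includes rescue tocolysis). Later latency was exponential with mean 20-120 days, capped near term. For gestational age at delivery ρ was 0.32-0.72:

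| SE unadjusted (days) | SE adjusted (days) | Variance cut |
|---|---|---|
| 3.14 | 2.18 | 1 − (2.18/3.14)² = 52% |
| 3.58 | 2.94 | 33% |
| 3.85 | 3.46 | 19% |
| 3.93 | 3.73 | 10% |

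Adjusted and unadjusted estimates had the same expected value.

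**Step 5: days until delivery.** In the same simulation its correlation with entry age was −0.05 to −0.28. The SE factor is √(1 − 0.28²) = 0.96 at best, a fall of 0-4%.

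**Step 6: what happens if women are lost before delivery.** Analysing only women with a known delivery date gave:

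| Assumed latency and loss | True difference (days) | Complete-case difference (days) |
|---|---|---|
| Exponential, means 25 vs 35 days; constant loss rate, mean time to loss 120 days (about 20% lost) | 10.0 | 6.4 |
| Same, mean time to loss 60 days (about 33% lost) | 10.0 | 4.5 |
| Step 4 model; random loss of 10-50% of women undelivered at 7 days | 4.8 | 5.0-5.8 |
| Step 4 model; all women undelivered at 7 days lost | 4.8 | 0.7 |

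The first row can be checked by hand: 1/(1/35 + 1/120) − 1/(1/25 + 1/120) = 27.1 − 20.7 = 6.4. The direction of the error depends on the pattern of loss.

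**The case against.** **The plan already holds a nearly equivalent comparison.** Days until delivery is delivery age minus entry age, so it removes entry age by subtraction. Where latency does not depend on entry age (b = 0), ANCOVA on delivery age has essentially the same precision as the unadjusted latency comparison. The largest gain in Step 2 (0.63) arises exactly there. This stands and limits the importance of the point. It does not make the unadjusted test a good choice for gestational age at delivery, which the plan reports as an outcome in its own right.

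**The sizes rest on assumptions.** They do. The article gives no SD or correlation, so only a range can be offered. That there is a gain follows from the sum itself, unless latency shortens week for week with entry age.

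**An unseen analysis plan may settle this.** For missing delivery dates that is a fair answer, and the article's silence is no fault. The choice of test, however, is stated in the article.

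**A stronger reading is tempting: that the planned tests are biased against the better arm.** A reader might infer this from the hospital-based form, supposing that women whose labour is stopped go home, deliver elsewhere and are dropped. The documents do not support it. They state no such loss and no rule that drops anyone, and the follow-up section commits to recording delivery details. Even if loss occurred, Step 6 shows that the bias could favour either arm. Leaving out entry age causes no bias under randomisation; the 0.34-week chance imbalance is ordinary sampling error, already inside the unadjusted standard error.

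**Survival methods are no full cure.** This stands too. If women are lost because treatment worked, censoring is informative. ANCOVA on delivery age also needs a known delivery.

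**Conclusion.** The concern holds as a matter of precision, for gestational age at delivery. The stated test is valid but inefficient: adjustment would cut the variance of the treatment difference by roughly 10-50%, assuming uniform entry over 25-34 weeks and the latency distributions above. The simple linear model reaches 63% in one corner, where the planned latency comparison already captures the gain.

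A reader might extend the precision argument to days until delivery. The figures do not support that: 0-4% in standard error is negligible. The only reason to change that analysis is a randomised woman with no known delivery date, and the documents do not say whether there will be any.

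Both outcomes are secondary. The primary 48 h comparison is unaffected, and nothing here calls for adjusting it.

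**What to change.** 1. **Gestational age at delivery:** name ANCOVA with treatment and gestational age at entry as the main analysis, and report the adjusted mean difference with its 95% confidence interval. Keep the unadjusted t-test or Mann-Whitney as a sensitivity analysis.
2. **Days until delivery:** state that if any randomised woman has no known delivery date, time to delivery will be analysed by Kaplan-Meier and Cox regression with censoring at last contact, so that she is not dropped. Report the number untraced by arm, and acknowledge that censoring may be informative. Tracing delivery dates protects both outcomes better than any model.
3. **Primary outcome:** no change on this ground.

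The cost is a few lines of text. The methods are available in SPSS, the covariate is already collected, and no extra patients are needed. Cox regression adds a proportional-hazards check. Because the trial is open-label, the change should be fixed before outcome data are analysed, so that it cannot look chosen after the event.
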